**LIST OF ABBREVIATIONS AND RELEVANT DEFINITIONS**

| **ABR** | **ABR form (General Assessment and Registration form) is the application form that is required for submission to the accredited Ethics Committee (ABR = Algemene Beoordeling en Registratie)** |
| --- | --- |
| **AE** | **Adverse Event** |
| **AR** | **Adverse Reaction** |
| **CA** | **Competent Authority** |
| **CCMO** | **Central Committee on Research Involving Human Subjects** |
| **CV** | **Curriculum Vitae** |
| **DSMB** | **Data Safety Monitoring Board** |
| **EU** | **European Union** |
| **EudraCT** | **European drug regulatory affairs Clinical Trials GCP Good Clinical Practice** |
| **IB** | **Investigator’s Brochure** |
| **IC** | **Informed Consent** |
| **IMP** | **Investigational Medicinal Product** |
| **IMPD** | **Investigational Medicinal Product Dossier** |
| **METC** | **Medical research ethics committee (MREC); in Dutch: medisch ethische toetsing commissie (METC)** |
| **(S)AE** | **Serious Adverse Event** |
| **SPC** | **Summary of Product Characteristics (in Dutch: officiële productinfomatie IB1-tekst)** |
| **Sponsor** | **The sponsor is the party that commissions the organisation or performance of the research, for example a pharmaceutical**  **company, academic hospital, scientific organisation or investigator. A party that provides funding for a study but does not commission it is not regarded as the sponsor, but referred to as a subsidising party.** |
| **SUSAR** | **Suspected Unexpected Serious Adverse Reaction** |
| **Wbp** | **Personal Data Protection Act (in Dutch: Wet Bescherming Persoonsgevens)** |
| **WMO** | **Medical Research Involving Human Subjects Act (Wet Medisch-wetenschappelijk Onderzoek met Mensen** |

# SUMMARY

**Rationale:** In sight of the upcoming dementia epidemic it is of vital importance to diagnose dementia accurately and early and to optimize care for home dwelling dementia patients and their informal caregivers. At present, diagnosis and management of dementia in primary care are suboptimal. Previous studies suggest that the combination of training providers, deploying a care coordinator and structuring collaboration among care providing organisations could improve the recognition of dementia; the quality of subsequent care for home dwelling dementia patients and their wellbeing. Cost effectiveness was not yet assessed.

**Research questions:**

1) To what extent does pro-active case finding of Mild Cognitive Impairment (MCI) and dementia increase the number of diagnoses in patients suspected of cognitive impairment by family physicians (FPs)?

2) To what extent does case finding and subsequent collaborative care improves the quality of care in patients diagnosed with mild cognitive impairment (MCI) or dementia diagnoses?

3) Do case finding and subsequent collaborative care improve the wellbeing, meet the information needs and decrease worrying of patients diagnosed with dementia or mild cognitive impairment (MCI) and their relatives?

4) What is the accuracy of FPs’ classification of the presence and absence of cognitive impairment in their older patients ≥ 65 years?

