**Setting and Study population:**

The cluster RCT is executed in 16 primary care practices (PCPs) among 312 patients ≥ 65 years in whom FPs suspect cognitive impairment.

The diagnostic accuracy study is executed among 312 patients labelled ‘possible cognitive impairment’ and in 100 patients labelled ‘no signs of cognitive impairment’ by FPs.

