## Exclusion criteria

1. Patients allready diagnosed with dementia.
2. Patient or (if present) caregiver terminally ill.
3. Permanent admission of the patient to a nursing home expected within 6 months.
4. The patient is not/no longer sufficiently capable of understanding spoken language or expressing him- or herself.

Diagnostic Test Accuracy Study: In order to also get information about the negative predictive value of the FPs cognitive classification, an additonal sample will be drawn of patients FPs classified as ‘no signs of cognitive impairment’ (Figure 2).

The study population for the process evaluation of succes and failure factors of the intervention consists of FPs and practice nurses in the intervention group. In addition, a random selection of patients and caregivers in the intervention group is invited to participate in a semi-structured interview.

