## Sample size calculation

In order to come to a sample size that would allow showing significant differences in quality of care, in wellbeing and in numbers of new dementia diagnoses we performed several power calculations:

Quality of care:

The primary outcome is the difference in total score on a set of quality indicators (QIs) after 12 months between intervention and control group. Perry et al. found a mean (crosssectional) concordance to the total set of 45.3% (SD 30.4). A serial measurement is not yet done with this set of QIs.

For this study we expect an increase in concordance in the intervention group of around 1.5 times the baseline scores. In other words; an added 22,5% concordance with the total set of QIs is considered as clinically relevant. We based out powercalculation on the method described by Kerry et al.(Kerry and Bland 1998). To be safe we assumed a somewhat larger within cluster SD of 35 than Perry et al. found. Based on research of Campbell et al on ICCs in primary care research we assumed a between cluster SD of 3(Campbell et al. 2005).

With an α of 0.05 and β of 0.90, a sample size of 5 clusters per arm and 72 patients per arm is required to show a statistically significant and clinically relevant difference in quality of care.

Caregiver wellbeing:

We chose the GHQ12 as a meausure of caregiver mental health as the most important patient and caregiver wellbeing measure. We expect to find results after a period of 12 months on this outcome. We based our sample size for the GHQ 12 on a study of Diaz et al . in 2008. They report a significant difference in GHQ 12 decline between intervention and control group. The average difference in decline was 2.2 points in a period of 6 months. Based on their SDs we (conservatively) estimated SDs in the control- (4.3) and interventiongroup (3.6). Based on the formula: √(SDbaseline2 x SDfollow-up2).

A paired t-test for average difference with unequal variance shows that assuming an equal distribution over intervention and controlgroup,a desired power of 90%, and an alpha of 0.05 we need to include 57 caregivers per group in order to find significant and clinically relelvant results (SASsoftware). Estimating that about half of patients will have an informal caregiver and that about 20% will be lost to follow-up in the first year and adding 10 % for clustering resulted in a desired sample of 156 patients per arm.

Number of new dementia diagnoses in 12 months:

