We based this calculation on a previous study on an educational intervention to improve the number of dementia diagnoses in primary care(Perry et al. ). Perry et al. conducted a cluster RCT design in which they asked 105 FPs to select 5 patients in whom they suspected cognitive impairment. FPs collaborated with a practice nurse in diagnosing dementia. In the intervention group, dementia was diagnosed in 49.1% (130 new diagnoses in 265 patients at risk) of these patients, in the control group in 14.8% (20 new diagnoses in 135 patients at risk) of these patients, after one year. Using the probabilities of Perry et al. and assuming a power of 90%, 20% loss to follow-up and adding 10% for clustering within practices resulted in a desired sample of 55 patients per arm.

Diagnostic accuracy of FPs’ classification at baseline

The diagnostyic accuracy is expressed in the positive and negative predictive value of the FPs at baseline. When we include 312 patients, initially classified by the FPs as cognitive impaired as well as and100 patients initially classified with no cognitive impairment, we reach a confidence interval of 17.9% around the point estimate, assuming a prior positive predictive value of 30%.

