**Control group**

8 PCPs

- Outcomes in patients with a baseline diagnosis MCI or dementia on the CAMCOG and their informal caregiver

(n ~ 156)

- Patient and caregiver characteristics and outcomes (n =156)

- CAMCOG (n =156)

- CAMCOG (n = 156)

- Quality of care indicators, diagnostic (N=156) & management indicators in patients with dementia (n ~ 50)

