**Appendix 2. overview of QIs, measured at baseline and at 12 months**

| **Process indicators (diagnosis)** |
| --- |
| 1. IF signs of dementia are noticed, THEN the general practitioner should start cognitive diagnostic workup within 3 months |
| 2. IF cognitive diagnostic workup has been started, THEN a ‘‘history from other sources’’ should be obtained. |
| 3. IF cognitive diagnostic workup has been started, THEN general physical examination should be conducted. |
| 4. IF cognitive diagnostic workup has been started, THEN neurological examination should be conducted. |
| 5. IF cognitive diagnostic workup has been started, THEN a blood test (at least erythrocyte  sedimentation rate, hemoglobin, mean corpuscular volume, creatinine, thyroidstimulating hormone, glucose) should be conducted. |
| 6. IF cognitive diagnostic workup has been started, THEN a cognitive screening test should be conducted. |
| 7. IF cognitive diagnostic workup has been started, THEN a mood screening test should be conducted. |
| 8. IF cognitive diagnostic workup has been started, THEN the patient’s physical, emotional and social needs should be assessed. |
| 9. IF cognitive diagnostic workup has been started, THEN the caregiver’s burden and needs should be assessed. |
| 10. IF a dementia diagnosis has been made, THEN it should meet the DSM-IV criteria.  1. Memory disorder  2. Other cognitive function disorder  3. Negative influence on daily functioning  4. Absence of a delirium |
| 11. IF a diagnosis has been made after cognitive diagnostic workup, THEN the general practitioner should disclose the diagnosis to patient and caregiver. |
| 12. IF a patient meets one of the following criteria, THEN the general practitioner should refer the patient to a multidisciplinary memory clinic.  1. Uncertainty about the diagnosis  2. Dementia diagnosis was made, and patients showed the following characteristics.  a. The course of the dementia was stepwise or rapidly progressive.  b. Characteristics that suggest rare types of dementia, like focal of frontal features or visual hallucinations in early stages of the dementia  c. Symptoms or results that suggest disorders that can only be treated by a specialist  d. Patient younger than 65  3. Patients or caregivers wish to start pharmacological treatment to ease dementia symptoms (cholinesterase inhibitors)  4. Patient’s or caregiver’s request to confirm the diagnosis |

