| 13. IF a dementia diagnosis has been made, THEN the general practitioner should formally bring the cognitive evaluation to a close, reviewing the following items.  1. Explicit disclosure of the diagnosis  2. Information about the prognosis  3. Offering leaflets, written information on dementia  4. Suggestions on home care  5. Information on possibilities of cholinesterase inhibitor treatment in dementia  6. Driving abilities |
| **Process indicators (follow-up)** |
| 14. IF a dementia diagnosis has been made, THEN an individualized care plan for the patient should be formulated. |
| 15. IF a dementia diagnosis has been made, THEN an individualized care plan for the caregiver should be formulated. |
| 16. IF a dementia diagnosis has been made, THEN the care plan should be evaluated and if necessary updated every 3 months. |
| **Structure indicators** |
| 17. Cognitive diagnostic examination consists of at least two face-to-face consultations. |
| 18. The general practitioner is the first contact point or will delegate this task to the practice nurse. |
| 19. A guidebook, listing all social services for dementia patients and their caregivers, is available in the family practice. |
| 20. General practitioners and practice nurses use the same medical record. |
| **Outcome indicators** |
| 21. Continuity of care (indicators 16, 19, AND 21 complied with = 16, 18, 20?) |
| 22. Number of emergency consultations in dementia patients |
| 23. Satisfaction of the patient and the informal caregiver was assessed, using a validated questionnaire |

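### Most indicators in the primary quality-of-care score depend on a work-up or diagnosis that the intervention is meant to cause, and the protocol disagrees with itself on which patients are scored

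*Protocol*

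**What the plan says.** Section 4.4 defines the main endpoint: "The primary outcome is the difference in total score on a set of quality indicators (QIs) after 12 months between intervention and control group". The 23 indicators are in Appendix 2. Three places bear on who contributes to that score.

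- **Research question 2** asks to what extent the intervention "improves the quality of care in patients diagnosed with mild cognitive impairment (MCI) or dementia diagnoses".
- **Appendix 2** words most indicators conditionally. QI 6 reads "IF cognitive diagnostic workup has been started, THEN a cognitive screening test should be conducted", and QI 14 reads "IF a dementia diagnosis has been made, THEN an individualized care plan for the patient should be formulated". QI 1 depends only on signs having been noticed, QIs 18-20 describe the practice, and QI 23 has no condition.
- **Figure 2** assigns the diagnostic indicators to N=156 in each arm. The same line goes on to "management indicators in patients with dementia (n ~ 50".

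The trial is run "among 312 patients ≥ 65 years in whom FPs suspect cognitive impairment", and section 4.3 excludes "Patients allready diagnosed with dementia". Section 4.4 takes its diagnosis rates from an earlier educational trial: 49.1% with the intervention and "in the control group in 14.8% (20 new diagnoses in 135 patients at risk) of these patients". Under Usual care in section 5.1, the protocol expects control family physicians (FPs) to be more reluctant to diagnose. It does not say how an indicator is scored when its IF condition is not met.

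**The concern.** The intervention is case finding. A nurse invites every suspected patient, and an FP work-up follows where her assessment points to MCI or dementia. It therefore acts directly on the events that decide whether most indicators apply. Because known dementia is excluded, every FP diagnosis of dementia in the trial is made after randomisation.

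If indicators count only when their condition is met, control patients enter mainly when their FP chose to act. They are likely to be the more evident cases, or the patients of more active FPs. A suspected patient who never gets a work-up, which is the shortfall in care that the trial sets out to reduce, would drop out of most of the score. A real gain could then show as nothing or as a loss, or a difference in case mix could pass for better care. Section 9.3 adjusts for baseline imbalance, but adjustment for measured covariates does not restore groups whose membership is itself a result of treatment.

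**Working it through.** **1. The planned size.** Inputs from section 4.4: difference 22.5 points, within-cluster SD 35, between-cluster SD 3, alpha 0.05 (taken as two-sided), and a stated beta of 0.90 read as 90% power. With 5 clusters per arm and 72/5 = 14.4 patients per cluster:

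SE = sqrt(2 × (3² + 35²/14.4)/5) = 6.13, and 22.5/6.13 = 3.67.

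Power is 89.3% (noncentral t, 8 df); 74 per arm would reach 90.0%. The stated 72 per arm therefore reproduces. It assumes one score for every patient.

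**2. How many indicators are conditional.**

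| Condition | QIs | Count |
|---|---|---|
| Work-up started | 2-9 | 8 |
| A diagnosis after work-up | 11 | 1 |
| Dementia diagnosed | 10, 13-16 | 5 |
| Referral criteria, mostly presupposing work-up or diagnosis | 12 | 1 |

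That is 14 of 23 on a work-up or diagnosis, or 15 with QI 12. QIs 17, 21 and 22 depend in effect on a diagnostic examination, on QI 16, or on being a dementia patient, which makes about 18. QIs 1, 18-20 and 23 are free of such conditions. Every enrolled patient arguably meets the condition of QI 1 through the first inclusion criterion.

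**3. Who is scored.** Research question 2 says diagnosed patients. Figure 2 says all 156 per arm for the diagnostic indicators and patients with dementia for the management indicators. Appendix 2 says those with a started work-up, or those with a diagnosis, item by item. These are different populations.

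**4. Size of the diagnosed groups at the protocol's rates.** 156 × 0.491 = 76.6 and 156 × 0.148 = 23.1. Over 8 control practices that is 23.1/8 = 2.9 diagnosed patients each. With 20% loss, 61 and 18 remain.

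**5. Precision in that subset.** This assumes that the same 22.5 points and SDs apply. With 8 practices per arm:

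SE = sqrt(2 × 3²/8 + 35² × (1/77 + 1/23)) = 8.45.

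Power is 76% (normal) or 70% (t, 14 df). With 61 v 18 it is 66% or 60%. With all 156 per arm scored, SE = 4.24 and power exceeds 99%.

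**6. Selection with no true effect (illustration).** Assume that diagnosis picks the upper tail of a normal latent severity that correlates r with the score. The mean severity of the top fraction p is φ(Φ⁻¹(1−p))/p. That is 0.81 SD for p = 0.491 and 1.56 SD for p = 0.148, a gap of 0.75 SD. The spurious difference is r × 0.75 × SD:

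- SD 30.4: 2.3 points at r = 0.1, 11.4 points at r = 0.5.
- SD 35: 2.6 points at r = 0.1, 13.1 points at r = 0.5.

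The sign of r sets the direction. The target is 22.5.

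**7. Effect of the scoring rule (illustration).** Assume that work-up is started in 90% v 40%.

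- Each element done in 70% of started work-ups in both arms: dropping unmet conditions gives 70 − 70 = 0 points. Counting them as not met gives 0.9 × 70 − 0.4 × 70 = 63 − 28 = 35 points.
- Elements done in 70% v 85%, because only evident control cases are worked up: dropping gives −15 points; counting as not met gives 63 − 34 = +29 points.

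**The case against.** The strongest reply is that the protocol never says unmet conditions are dropped. Figure 2 gives the diagnostic indicators the full 156 per arm, and section 4.4 compares the total score between the arms. How to score an unmet condition is commonly left to a statistical analysis plan, which is not at hand here. Section 9.3 lists patients with baseline CAMCOG below 86 as an additional analysis, which suggests that the main one covers everybody. Research question 3 also speaks of diagnosed patients, and Figure 2 turns that into a baseline CAMCOG diagnosis; question 2 could be read in the same way.

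Much of this stands. A reader might infer that the whole primary outcome is confined to patients who reached a work-up or a diagnosis. Appendix 2 and Figure 2 do not support that.

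A reader might also infer that the n ~ 50 per arm is an error for 77 and 23, since the mean of those two is 50. That is not established. Section 4.4 assumes a positive predictive value of 30% against the CAMCOG, and 156 × 0.30 = 47 in each arm, which explains an equal n ~ 50 at least as well. That reading is also an inference, because the CAMCOG reference covers dementia or MCI.

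What the reply does not remove is the conflict within the protocol. An analysis plan can add a scoring rule, but it should not have to choose among the populations of the research question, the figure and the indicator wording. QIs 10 and 13-16 are worded on a diagnosis having been made, not on a CAMCOG result.

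**Conclusion.** The point holds in a conditional form. Fourteen of 23 indicators have denominators set after randomisation by events that the intervention is designed to produce, and the protocol gives inconsistent populations for its primary comparison. If unmet conditions are dropped, or the comparison is confined to FP-diagnosed patients, the arms are not randomised groups. They would hold about 77 and 23 patients, and power would fall to about 70-76% before losses.

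The bias could run either way. The 2 to 13 points from selection and the 35 to 44 points between scoring rules (35 − 0; 29 − (−15)) rest on assumed correlations, work-up rates and completion rates, so they show scale and are not forecasts.

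It would go too far to say that the randomised comparison is already lost. If all 156 per arm are scored on QIs 2-9 with unmet conditions counted as not met, those items are free of this selection.

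**What to change.** - State that the primary comparison uses all sampled patients in both arms (156 per arm, as Figure 2 already shows for the diagnostic indicators). For QIs 1-9, count no work-up started as not met, alike in both arms.
- Compare the management indicators in a group defined at baseline in the same way in both arms, using the baseline CAMCOG. First reconcile Figure 2, which shows the CAMCOG in both arms, with the Appendix 3 footnote that limits it to the intervention arm. Say whether the group is dementia or also MCI, because QIs 13-16 concern dementia only and an undiagnosed MCI patient should not count as a failure on them.
- Give a rule for QIs 10, 11 and 13, which Appendix 2 files under diagnosis although they depend on one.
- Report results among FP-diagnosed patients as descriptive only, and reword research question 2 to match.
- State the basis of n ~ 50. If it means FP-diagnosed dementia, the protocol's rates give about 77 and 23; if it means the baseline CAMCOG, say so.

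**Cost.** This takes protocol wording and a scoring rule, with no extra patients. No new data are needed provided that the CAMCOG is in fact done at baseline in both arms. Absolute concordance will fall below the 45.3% planning value, partly because the staged work-up in Appendix 1 leaves some elements undone by design in screen-negative patients. The 45.3% mean, the SD and the 22.5-point target must therefore be rechecked for the new scoring. There is room for this, since 156 per arm is well above the 72 required.

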**Setting and Study population:**

The cluster RCT is executed in 16 primary care practices (PCPs) among 312 patients ≥ 65 years in whom FPs suspect cognitive impairment.

The diagnostic accuracy study is executed among 312 patients labelled ‘possible cognitive impairment’ and in 100 patients labelled ‘no signs of cognitive impairment’ by FPs.

**Study design:**

Ad 1-3) Cluster Randomised Controlled Trial.

Intervention: collaborative diagnostic evaluation and management.

A trained practice nurse invites patients with suspected cognitive impairment for a comprehensive geriatric assessment, including a cognitive screening. If this assessment suggests the presence of MCI or dementia, it is followed by a more thorough assessment, including physical and neurological examination and laboratory tests, by the FP. When this results in a MCI or dementia diagnosis, the practice nurse in close collaboration with the FP will offer patients collaborative care. This consists of psycho education and support. In addition the practice nurse according to their needs as identified will coordinate care after a geriatric assessment.

Controls: Care as usual will be offered by the FP.

Ad 4) Diagnostic Test Accuracy Study: cross-sectional comparison of FPs’ recollections of the presence or absence of cognitive impairment in their patients ≥ 65 years, with reference standard diagnoses on the presence or absence of MCI or dementia.

**Main study parameters**

Ad 1-2 (b) 23 quality indicators: 13 on the diagnostic process, 3 on follow-up care, 4 on structure of care and 3 on outcomes after 12 months.

(a) The number of MCI and dementia diagnosis after 12 months.

Ad 3. Patient: Quality of life (EQ5D, QoL-AD); mental wellbeing (MH5); worrying (…), information needs (…). Caregiver: mental health (GHQ 12); burden (SSCQ); quality of life (EQ-5D); worrying (..), information needs (…) over 12 months.

Ad 4. Diagnostic accuracy of FPs’ cognitive classification of individuals compared to the reference standard (CAMCOG) diagnosis at baseline.

**Nature and extent of the burden and risks associated with participation, benefit and group relatedness:** The interventions done within the context of the study are regarded to be of no risk to the patients and caregivers exposed to them. We aimed to minimise the burden placed on dementia patients and their caregivers by limiting the interviews with patients and carers (and questionnaires for carers) to twice a year.

